# Comparison of live birth rates between calorie-restricted diet and metformin prior to ovulation induction therapy in women with polycystic ovary syndrome and overweight/obesity: a protocol for a multicenter, randomized comparative effectiveness trial

**DOI:** 10.3389/fpubh.2026.1881719

**Published:** 2026-09-10

**Keywords:** calorie-restricted diet, live birth, overweight and obesity, polycystic ovary syndrome, randomized comparative effectiveness trial

## Abstract

**Background:**

Polycystic ovary syndrome (PCOS) significantly impairs physical and mental health, quality of life, and fertility in women of reproductive age. Strategies to enhance fertility in PCOS have been prioritised in International Guidelines. Whilst Guidelines recommend Letrozole in first line ovulation induction (OI), therapeutic interventions to optimise endocrine and metabolic PCOS features prior to OI have not been adequately researched despite potential to improve live birth and pregnancy outcomes. Whilst both a calorie-restricted (CR) diet and metformin interventions may offer benefits in the context, evidence is limited including for live birth rates, and pregnancy outcomes. Therefore, this study will aim aims to compare the effects of a CR diet versus metformin on live birth, endocrine, reproductive, and metabolic parameters as well as pregnancy outcomes in women with PCOS and overweight/obesity.

**Method:**

This multicenter, randomized (1:1) comparative effectiveness trial will evaluate and compare the effects of a CR diet versus metformin, administered for 12 weeks prior to OI, on live birth, endocrine, metabolic, reproductive, and pregnancy outcomes in women with PCOS and overweight/obesity. The primary analysis will follow the intention-to-treat principle, including all participants who underwent randomization.

**Discussion:**

This trial investigates the comparative efficacy of a CR diet versus metformin over a 12-week period prior to OI therapy in women with PCOS and overweight/obesity. Early therapeutic intervention holds significant potential to disrupt the pathophysiological cycle characterized by hyperandrogenism, excessive adiposity, and insulin resistance for improving fertility and pregnancy outcomes.

**Clinical trial registration:**

ClinicalTrials.gov, identifier NCT06049186.

## Introduction

Polycystic ovary syndrome (PCOS), a prevalent endocrine and reproductive disorder, significantly impairs the physical and mental health as well as the quality of life in women of reproductive age, with a prevalence reaching up to 12% (1–3). Notably, the global burden of PCOS is escalating at an alarming rate, establishing it as a significant public health challenge (4). PCOS is an endocrine condition with increased insulin resistance, hyperandrogenism, and elevated anti-Müllerian hormone levels. Key clinical manifestations include reproductive (menstrual irregularities, infertility, and high risk pregnancy) (5), metabolic (overweight/obesity, diabetes, and cardiovascular disease) (6–8) alongside psychological and dermatological features (2). These factors may independently or synergistically contribute to diminished fertility in women with PCOS, recognized as the leading cause of anovulation infertility, where infertility is clinically defined as the inability to achieve a clinical pregnancy after 1 year or more of regular, unprotected sexual intercourse (8). In recent years, strategies to enhance fertility in women with PCOS have garnered substantial attention and have become a critical focus in clinical research and practice.

The pathogenesis of PCOS remains incompletely elucidated, and genetic factors and environmental factors such as lifestyle and obesity have been implicated in its aetiology (9). PCOS is a markedly heterogeneous disorder, characterized by complex and variable clinical manifestations (10). It is frequently associated with significant metabolic abnormalities, a subset of which appear to be intrinsic to the syndrome yet are further exacerbated by excess adiposity, which also contributes to its increased prevalence (3, 11). Beyond its endocrine and metabolic manifestations, PCOS is associated with anxiety, depression, and eating disorders (12, 13). Therefore, PCOS should be conceptualized as both a metabolic, psychological and reproductive disorder.

Metformin, a well-established insulin-sensitizing agent, is extensively utilized in the management of endocrine and metabolic features in women with PCOS and overweight/obesity (14). In women with PCOS and obesity, metformin therapy has been demonstrated to improve insulin sensitivity, attenuate hyperinsulinaemia and lower circulating androgen concentrations, and improve menstrual regularity and ovulation rates (15–19). However, conflicting evidence regarding the efficacy of metformin has been reported, which may be attributed to heterogeneous treatment responses among specific patient subgroups (20, 21). In women with PCOS, the clinical limitations of metformin use are primarily related to gastrointestinal adverse effects, such as nausea, vomiting, abdominal pain, and diarrhea (15, 22). Long-term therapy has also been associated with vitamin B12 deficiency (15, 22). Approximately 5% of patients demonstrate intolerance to metformin therapy (23). These limitations highlight the need to develop alternative therapeutic strategies that offer improved safety and efficacy for managing PCOS and its associated metabolic complications.

Current international evidence-based guidelines for PCOS management strongly emphasize the critical role of dietary interventions in women with PCOS and overweight/obesity (14, 24). Dietary interventions have been demonstrated to improve endocrine, metabolic and psychological parameters in women with PCOS (25, 26), with the majority of population studies primarily focusing on weight-related indices, glycolipid metabolism, and hormonal profiles (27, 28). However, evidence concerning their effects on definitive reproductive endpoints, including pregnancy and live birth rates, remains limited (27, 28). Notably, the few existing dietary intervention trials suggest potential benefits in increasing pregnancy and ovulation rates, underscoring the need for further rigorous research to elucidate their impact on clinical fertility outcomes (27). Effective dietary management of PCOS necessitates a multidisciplinary approach encompassing dietitians, endocrinologists, reproductive specialists, and other healthcare professionals (29–31). Such interdisciplinary collaboration is crucial for addressing not only weight reduction but also endocrine and metabolic dysfunctions, as well as reproductive complications (29–31). Beyond these goals, this team-based strategy additionally aims to support psychological well-being, enhance patient motivation, and mitigate the pervasive adverse effects of weight stigma on both clinical care and patient self-perception (29–31). In parallel with lifestyle management, pharmacological options for obesity have expanded in recent years, particularly with the introduction of glucagon-like peptide-1 receptor agonists (32). These agents can produce substantial weight loss and improve metabolic parameters, and emerging evidence suggests potential benefits in women with PCOS and overweight/obesity (33). However, their use in women actively planning pregnancy is limited by considerations regarding use around conception and the need for treatment discontinuation before pregnancy. Therefore, effective non-pharmacological strategies for preconception metabolic management remain clinically important.

A calorie-restricted (CR) diet, as an effective strategy for weight loss and prevention of chronic metabolic diseases, may represent a promising non-pharmacological and non-surgical intervention for women with PCOS and overweight/obesity (34). Several studies have demonstrated that CR diets reduce abdominal adiposity and enhances insulin sensitivity. Furthermore, CR diets are associated with elevated serum sex hormone-binding globulin (SHBG) levels and decreased free androgen index (FAI) and testosterone (T) concentrations (35, 36). However, most previous studies have focused on metabolic outcomes or investigated dietary intervention in combination with metformin, and direct comparative evidence between CR diet and metformin remains lacking (37). Metformin was selected as the active comparator because it is a widely used insulin-sensitizing pharmacological intervention in women with PCOS and overweight/obesity, whereas CR diet represents a non-pharmacological approach that may target overlapping metabolic and endocrine abnormalities through energy restriction and weight loss. Comparing these two approaches before ovulation induction (OI) therefore provides a clinically relevant opportunity to determine whether metabolic optimization through CR diet can translate into improved reproductive outcomes relative to metformin. It remains unclear whether a CR diet can improve definitive reproductive outcomes, particularly live birth, compared with metformin when administered before OI. Recent evidence further suggests that individual reproductive characteristics, including age, BMI, and AMH, may contribute to variability in reproductive prognosis among women with PCOS undergoing fertility treatment (38, 39). Therefore, the primary objective of this trial is to determine whether a 12-week CR diet administered before OI is superior to metformin in improving the live birth rate in women with PCOS and overweight/obesity. We hypothesize that the CR diet will result in a higher live birth rate than metformin. The trial will additionally evaluate whether CR diet may provide an effective non-pharmacological strategy for metabolic and reproductive optimization before OI.

## Methods

### Study design

This multicenter, randomized (1:1) comparative effectiveness trial will be conducted to evaluate and compare metabolic and reproductive outcomes between a CR diet and metformin over a 12-week period prior to OI therapy in women with PCOS and overweight/obesity from numerous hospitals nationwide in China. Female participants meeting the predefined eligibility criteria will be recruited, after which eligible subjects will be randomly assigned to either the CR diet group or the metformin intervention group. Following the intervention, standard OI therapy will be administered to participants in both study groups, and subsequent pregnancy outcomes will be monitored. The study flow chart is illustrated in Figure 1. The trial protocol has been designed and is reported according to the Standard Protocol Items: Recommendations for Interventional Trials (SPIRIT) (see Supplementary Material), and the trial results will be reported in accordance with the Consolidated Standards of Reporting Trials (CONSORT). The study protocol has received ethical approval from the Ethics Committee of Shanghai First Maternity and Infant Hospital (Approval Number: KS23168). All procedures involving human participants are in accordance with the ethical standards of the institutional research committee. Written informed consent will be obtained from all participants prior to enrollment. This study was registered at ClinicalTrials.gov (NCT06049186) on 14 September 2023.

**Figure 1 fig1:**
[figure not shown]
Study flow chart. PCOS, polycystic ovary syndrome; CR, calorie-restricted.

### Aims of this study

#### Primary

To determine whether a 12-week CR diet administered prior to OI is superior to metformin in improving the live birth rate among women with PCOS and overweight/obesity. We hypothesize that the CR diet will result in a higher live birth rate than metformin.

#### Secondary

To compare the effects of a CR diet and metformin on secondary reproductive outcomes and changes in anthropometric, metabolic, and reproductive hormone parameters prior to OI in women with PCOS and overweight/obesity. Key secondary outcomes include pregnancy-related outcomes, body weight, glucose and insulin-related measures, lipid profiles, and reproductive hormone levels.

### Eligibility criteria

Inclusion criteria: (1) Women aged between 20 and 35 years, (2) body mass index (BMI) ≥ 23 kg/m^2^ based on the WHO Asian population criteria (40), (3) diagnosed with PCOS based on the Rotterdam diagnostic criteria, as updated in the 2023 International Evidence-Based Guideline for the Assessment and Management of PCOS (14). PCOS was diagnosed when at least two of the following three features were present: (a) oligo- or anovulation, (b) clinical and/or biochemical hyperandrogenism, and (c) polycystic ovarian morphology (PCOM) on ultrasound.

Exclusion criteria: (1) pre-existing type 2 diabetes mellitus, (2) uncontrolled thyroid disorders, (3) acute or chronic infections, (4) severe cerebrovascular or cardiovascular diseases or organic heart disease, (5) history of malignant tumors, (6) use of glucocorticoids or anti-androgen drugs (e.g., spironolactone, cyproterone acetate, flutamide, oral contraceptive pills) within the past 3 months, (7) congenital or acquired uterine anomalies, (8) prior bariatric surgery, (9) currently undergoing weight loss treatment and having experienced weight loss > 5% within the past 3 months, (10) severe hepatic or renal dysfunction, (11) tubal obstruction, (12) total number of motile sperm in male partner < 10 million.

### Sample size

According to the literature (41, 42), live birth rates among women with PCOS in the control arm were around 31.0%. Based on findings from other studies in fertility care and expert opinions from gynecologists and epidemiologists, we assume that a minimal clinically important difference to make CR preferable over conventional diet would be 15.0% (43). To detect this difference using a two-sided test with a 5.0% alpha error and 80% statistical power, and accounting for a potential dropout rate of 20% (44), the minimum numbers of participants required for the study will be 406. Participants will be randomized in a 1:1 ratio between the intervention and control groups. No interim analysis or sample size re-estimation is planned, and the prespecified sample size will be maintained throughout the trial. As the true intervention effect may differ from that assumed in the sample size calculation, the final treatment effect will be reported with its corresponding 95% confidence interval to indicate the magnitude and precision of the observed effect.

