For the primary outcome, participants who are lost to follow-up and whose live birth status cannot be ascertained will be conservatively classified as not having achieved a live birth. The number and reasons for withdrawal and loss to follow-up will be documented and reported separately for each treatment group. Missing baseline covariate data will be handled using complete-case analysis in the corresponding adjusted models. Multiple imputation will be used in sensitivity analyses to assess the robustness of the results to missing covariate data. Additional sensitivity analyses will be performed to evaluate the potential impact of missing outcome data and loss to follow-up on the primary findings. These analyses will examine alternative assumptions regarding outcomes among participants lost to follow-up and will be compared with the primary analysis in which missing live birth outcomes are classified as no live birth.

Participants with insufficient intervention adherence or protocol deviations will remain included in the primary intention-to-treat analysis according to their randomized treatment assignment. Additional sensitivity analyses will be conducted to assess the potential impact of major protocol deviations on the primary findings. A per-protocol analysis will be conducted as a supportive secondary analysis and will include participants who complete the trial, meet the prespecified intervention-specific adherence criteria, and have no major protocol violations. Primary and secondary outcomes will be compared between treatment groups within the per-protocol population. The per-protocol findings will be interpreted as supportive analyses alongside the primary intention-to-treat results. Secondary outcomes will be compared between groups using a similar approach for categorical variables. Mixed-effects models will be applied for repeated measurements. Exploratory subgroup analyses will be conducted according to prespecified baseline characteristics, including age and BMI. Potential heterogeneity in intervention effects across these characteristics will be assessed by including treatment-by-subgroup interaction terms in the corresponding regression models. Where AMH measurements are available, the potential effect-modifying role of AMH will also be explored in supplementary analyses.

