Several limitations of this study should be acknowledged. First, because of the distinct nature of the interventions, participants and personnel delivering the interventions cannot be blinded to treatment allocation, which may introduce performance bias. Nevertheless, outcome assessors and data analysts will remain blinded, and live birth, the primary outcome, is an objective clinical endpoint, which may reduce the potential for assessment bias. Second, the intensity of intervention differs between the two groups. Participants in the CR diet group receive app-based dietary monitoring, individualized dietary guidance, and regular feedback from dietitians, whereas participants in the metformin group receive pharmacological treatment with routine clinical advice. Consequently, observed between-group differences may partly reflect the additional healthcare attention, self-monitoring, and behavioral support provided as components of the CR intervention rather than calorie restriction alone. Attention bias therefore cannot be completely excluded, and the findings should be interpreted as reflecting the comparative effectiveness of the overall CR diet and metformin intervention strategies rather than the isolated physiological effects of calorie restriction versus metformin. Third, although standardized study procedures are used to promote consistency across participating centers, some center-level variability in intervention delivery and measurements cannot be completely excluded. In particular, differences in body composition assessment devices across centers may introduce measurement variability in anthropometric outcomes. Finally, the study population is restricted to women aged 20–35 years with PCOS and overweight/obesity who are eligible for OI, which may limit the generalizability of the findings to women outside this age range, women with PCOS without overweight/obesity, or those receiving other forms of fertility treatment. In addition, because the trial is conducted in China and applies an Asian-specific BMI threshold, extrapolation of the findings to populations with different ethnic, dietary, and healthcare backgrounds should be made cautiously.

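### The 406 assumes that dropouts leave the analysis, but the primary analysis keeps them as no live birth; if the whole planned 20% is unascertained, power is about 75%, not 80%

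*Protocol article*

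**What the plan says.** The Sample size section of the protocol article gives these inputs:

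- Control rate, in percent: "live birth rates among women with PCOS in the control arm were around 31.0".
- Difference sought, in percent: "minimal clinically important difference to make CR preferable over conventional diet would be 15.0". Read as an absolute difference, this puts the CR arm at 46%.
- Error rates: "two-sided test with a 5.0% alpha error and 80% statistical power".
- Attrition and total: "accounting for a potential dropout rate of 20% (44), the minimum numbers of participants required for the study will be 406", randomized 1:1. The section rules out sample size re-estimation.

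The Statistical analysis section makes intention-to-treat the primary analysis, with all randomized women in their assigned arm and a chi-square or Fisher's exact test on live birth. On missing outcomes it says that "participants who are lost to follow-up and whose live birth status cannot be ascertained will be conservatively classified as not having achieved a live birth". It also promises loss and its reasons by arm, and sensitivity analyses under other assumptions about the lost women.

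The limitations paragraph of the Discussion concedes that "the intensity of intervention differs between the two groups", with app monitoring and dietitian feedback in the CR arm only.

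**The concern.** The two sections treat a lost woman differently. In the sample size she leaves the denominator and the 15-point difference is untouched. In the primary analysis she stays in the denominator as a failure. The inflation by 1/0.8 therefore compensates for a loss of numbers that does not occur, while the dilution that does occur is not allowed for. At stake is whether the advertised 80% belongs to the test that will decide superiority.

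A second, smaller matter is the description of the missing-outcome rule as conservative. Equal loss shrinks the difference, so the label fits there. Unequal loss biases the comparison against whichever arm loses more women. That could work for or against CR, so the label is not safe as a general statement.

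**Working it through.** **1. The plan's own figure.** Inputs from Sample size: 31% versus 46%, two-sided 5%, 80% power, 20% dropout. With unpooled variance:

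n = (0.31×0.69 + 0.46×0.54) × (1.960 + 0.842)² / 0.15² = 0.4623 × 7.849 / 0.0225 = 161.3, so 162 per arm.

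162 / 0.8 = 202.5, so 203 per arm and 406 in total. This is an exact match. Multiplying by 1.2 instead gives 195 per arm, or 390, which does not match. If 162 per arm were analysed at 31% versus 46%, the pooled test would have 79.5% power, so 406 is sound for its own method.

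**2. The rule in the Statistical analysis section.** If a share d of each arm is unascertained and counted as no live birth, the analysed rates are 0.31(1−d) and 0.46(1−d), with all 203 per arm kept. At d = 0.20:

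- rates 0.8×0.31 = 0.248 and 0.8×0.46 = 0.368, a difference of 0.120;
- pooled rate 0.308, so the null standard error is √(2×0.308×0.692/203) = 0.0458;
- alternative standard error √((0.248×0.752 + 0.368×0.632)/203) = 0.0454;
- power = Φ((0.120 − 1.960×0.0458)/0.0454) = Φ(0.66) = 74.7%.

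Exact enumeration of the uncorrected chi-square test also gives 74.7%. With a continuity correction, which is close to Fisher's test, power is about 71%.

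**3. Dependence on the share counted as failures** (203 per arm, equal loss):

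| Share | Rates | Power, formula | Power, exact |
|---|---|---|---|
| 0% | 31.0% vs 46.0% | 87.7% | 87.5% |
| 10% | 27.9% vs 41.4% | 81.8% | 82.1% |
| 15% | 26.4% vs 39.1% | 78.4% | 78.6% |
| 20% | 24.8% vs 36.8% | 74.7% | 74.7% |

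Power reaches 80% at about 13% loss. The 0% row also covers the case where 31% and 46% already count losses as failures: no inflation was then needed, and power is about 88%.

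**4. Unequal loss, as illustration only.** The documents give no loss by arm. Assume 25% on metformin, 15% on CR, no true effect, and lost women with the same underlying live birth rate as the rest:

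- true rate 31%: analysed rates 23.25% vs 26.35%, a spurious +3.1 points for CR; exact two-sided type I error 11.2%;
- true rate 46%: 34.5% vs 39.1%, +4.6 points; 16.0%.

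A milder split of 22.5% versus 17.5% gives 6.6% and 7.7%. Exchanging the arms gives the same error rates with the bias against CR.

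**The case against.** The strongest reply is that dropout is not the same as an unknown outcome. The rule scores as failures only lost women whose status cannot be established. The outcome section confirms live birth from hospital records, and women who stop the diet or the tablets stay in the analysis. Some of the 20% may well have a known outcome, and if half do, power is about 82%. This stands: 75% is the figure at the plan's full dropout rate, not a forecast. It does not rescue the stated 80%, because the Sample size section never separates dropout from unascertained outcome.

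A reader might infer that the primary test fails to hold its 5% error rate. The documents do not show that. No section gives loss by arm, and the Discussion's remark on intensity concerns attention bias, not retention. Twice-weekly feedback stops after 8 weeks and both interventions stop at week 12, whereas live birth follows up to five ovulation induction cycles common to both arms. The CR arm's energy restriction and daily recording could equally raise its own loss. If women who leave conceive less often than those who stay, the distortion is smaller too.

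The plan already includes sensitivity analyses under alternative assumptions and reporting of loss by arm. These answer much of the bias question but do not alter the power of the primary test.

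**Conclusion.** The point holds as a mismatch between two sections. The 406 is arithmetically right for an analysis that excludes dropouts, and the primary analysis does not exclude them. The shortfall is about 5 percentage points of power (74.7% against 80%) under three assumptions: the whole 20% is unascertained live birth, loss is equal in both arms, and 31% and 46% are rates in women with known outcome. The division by 0.8 implies the third, but the text does not state it.

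It would be too strong to say that the trial is underpowered on every reading. Power exceeds 80% when loss stays below about 13%, and is about 88% if the assumed rates already absorb losses.

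The word *conservatively* is unsupported as a general claim, since the direction of bias depends on which arm loses more women. The 11% to 16% type I error illustrates an assumed split and is not a finding about this trial.

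**What to change.** 1. **Sample size.** State whether 31% and 46% count losses as failures. Give the power for the planned rule. If they are rates in women with known outcome, suitable wording is: *With 203 women per arm and unascertained outcomes counted as no live birth, power is about 82%, 79% and 75% when 10%, 15% and 20% of each arm are unascertained.*

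2. **Statistical analysis.** Delete *conservatively*. Specify that one of the sensitivity analyses already planned varies the assumed live birth rate among lost women separately in each arm.

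Making multiple imputation the primary method is optional. It should not be combined with the wording above, which would then describe a superseded analysis; it would need its own power statement.

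The cost is a few sentences and a little programming, with no extra patients. The downside is a less favourable stated power. The changes should be made before unblinding.
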